### Participant timeline {13}

See the enclosed flowchart (Additional file 4).

### Sample size {14}

Sample size calculation for the primary outcome was performed using an online calculator (https://www.sealedenvelope.com/power/binary-noninferior/) based on results of a previous study [3] that demonstrated a CVS incidence of 10% after tCDC insertion in the internal jugular vein. The rate of stenosis events in historical data has ranged from 10% for the jugular vein to 42% for the subclavian vein. Given the perceived and shown advantages with subclavian lines (less infections/thrombosis, more comfortable for the patient during insertion and use), we chose a 15% noninferiority margin as this is less than half the absolute difference, is judged to be clinically acceptable and results in a reasonable sample size. Calculations revealed that 50 patients per group are needed to be 80% sure that the upper limit of a one-sided 95% confidence interval (or equivalently a 90% two-sided confidence interval) will exclude a difference in favour of the standard group. In order to have 100 patients perform the CT venography for the per-protocol analysis, at least 200 patients will probably have to be included in the trial. Important differences found between the treatment groups (in terms of how many that did not complete the protocol) will be reported.

### Recruitment {15}

Patients will be recruited consecutively and will be identified by the doctor on call or by the dedicated nurse responsible for the tCDC insertion logistics at each site. As inclusion is dependent on an available study operator, each site will encourage CVC-inserting physicians to embrace the described technique and to participate in the educational session to fulfil the prerequisites to be able to enrol and insert tCDCs within the study.

## Assignment of interventions: allocation

### Sequence generation {16a}

Patients will be randomised and stratified for each centre. In addition, the randomisation will be performed in blocks with varying size (2, 4 and 6). The randomisation will be performed in REDCap (Research Electronic Data Capture, Nashville, TN, US), a browser-based, metadata-driven electronic data capture software [13] that will be used both for randomisation and as an eCRF.

### Concealment mechanism {16b}

None of the physicians performing the tCDC catheterisations will have access to the randomisation file.

### Implementation {16c}

The allocation sequence file will be generated by a researcher not affiliated to the project. Enrolment and assigning participants to interventions will be performed as previously described.

## Assignment of interventions: blinding

### Who will be blinded {17a}

The radiologist that assesses the primary outcome, i.e. interpreting CT venographies and the physician that performs the ultrasound/Doppler investigation in conjunction with the CT venography, will be blinded to study group allocation. In addition, the person who performs the statistical analyses will be blinded. The patient, the inserting physicians and other care providers are unable to be blinded.

### Procedure for unblinding if needed {17b}

Procedures for unblinding are not applicable for the current study.

## Data collection and management

### Plans for assessment and collection of outcomes {18a}

Electronic case report forms will be used for collection of all necessary data. Files showing the eCRFs used in the trial are available upon request.

### Plans to promote participant retention and complete follow-up {18b}

If needed, patients will receive an appointment at the department for nephrology after the tCDC removal. At this appointment, the patient will be assessed by the responsible nephrologist with regard to contraindications to perform a CT venography. Furthermore, the patient will be informed about the main benefit of performing a CT venography: mapping of the venous system, which is valuable when future need of central venous and/or dialysis access arises.

If a physical appointment is impossible or deemed unnecessary, a nephrologist or a dedicated study physician will review patient records and labs to ensure there are no contraindications to perform a CT venography.

Regarding outcomes that may be collected for patients that do not complete the follow-up, please see the “Criteria for discontinuing or modifying allocated interventions {11b} section.”

### Data management {19}

Randomisation and data collection will be performed using an eCRF within REDCap, a secure web application. Randomisation, data collection and entry in the eCRF are performed both by dedicated research nurses and by the investigators. Data quality is promoted in the eCRF, e.g. by range checks. Paper forms are used for patient questionnaires and dialysis protocols and will be scanned into the eCRF by dedicated research nurses and later transferred to the main database.

### Confidentiality {27}

All data will be stored and handled according to the Swedish data protection regulation. Study participants will be identified by a study number in REDCap to ensure confidentiality. The code linking a study number to a specific patient will be stored in a computer in a secure location within the hospital premises. REDCap access will be restricted to site investigators and research nurses. Anonymous trial data may be shared with other researchers in the future to enable international prospective meta-analyses.

### Plans for collection, laboratory evaluation and storage of biological specimens for genetic or molecular analysis in this trial/future use {33}

No biological specimens will be collected in the current study.

## Statistical methods

### Statistical methods for primary and secondary outcomes {20a}

The study aims to explore if the incidence of post-catheterisation CVS when using the right-sided subclavian route is non-inferior to the internal jugular route. All patients randomised in this trial will be analysed on a per-protocol basis. The primary outcome will thus be analysed only in patients subjected to the follow-up CT venography. Patients will be enrolled using previous exit rates to determine when the calculated sample size for both groups can be reached.

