**Methods:**

Adult patients needing a tCDC will be included from several hospitals and randomised to either subclavian or internal jugular vein catheterisation with a silicone tCDC. Inclusion continues until 50 patients in each group have undergone a follow-up CT venography. The primary outcome is the incidence of post-catheterisation central vein stenosis detected by a CT venography performed 1.5 to 3 months after removal of the tCDC. Secondary outcomes include between-group comparisons of (I) the patients’ experience of discomfort and pain, (II) any dysfunction of the tCDC during use, (III) catheterisation success rate and (IV) the number of mechanical complications. Furthermore, the ability to detect central vein stenosis by a focused ultrasound examination will be evaluated using the CT venography as golden standard.

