### Reasons to exit the trial

Inability to place the catheter in the randomised vein for any reason (the catheter may then be placed in any vein at the discretion of the operator)Inability to achieve a correct catheter tip locationPatient desires to no longer take part in the trial

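### The non-inferiority claim rests only on a per-protocol set expected to hold about half of the randomised patients, with no committed analysis by allocated vein to test it

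*Protocol article*

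**What the plan says.** Section {20a} fixes the analysis set: "All patients randomised in this trial will be analysed on a per-protocol basis", and then "The primary outcome will thus be analysed only in patients subjected to the follow-up CT venography". Sections {11b} and {14} also speak of a per-protocol analysis, and no other set is named. The Data Availability section describes the article as the full protocol, so this is a stated choice and not a detail left open.

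Section {14} derives 50 analysed patients per group and adds that "at least 200 patients will probably have to be included in the trial".

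Patients are lost at two points after randomisation:

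- **Exit from the trial** (Reasons to exit the trial): "Inability to place the catheter in the randomised vein for any reason", failure to reach a correct tip location, or the patient's wish to leave.
- **Exclusion from the primary analysis** (Reasons for exclusion from primary outcome analyses): no follow-up CT (including death, or low eGFR without dialysis), dwell under 7 days, or another catheter in a right-sided study vein before the CT.

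The mitigations are:

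- reasons for exit and exclusion are collected and reported (section {11b});
- important between-group differences in non-completion are reported ({14});
- baseline imbalance is checked, with a stratified comparison if needed ({20b});
- best–worst and worst–best scenarios may be considered if missing data cannot be ignored ({20c}).

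**The concern.** Randomisation makes the two groups comparable at the moment of allocation. Here about half of each group is expected to leave afterwards, and the document itself gives grounds for thinking that some departures relate to route or outcome. The Background cites misplacement of 1.4% for the right internal jugular and 9.1% for the right subclavian vein, and failure to reach a correct tip position is an exit. It also lists earlier catheter removal among the consequences of stenosis in haemodialysis patients, while short dwell is an exclusion. That statement is general, so it supports a mechanism without proving one in this trial.

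A per-protocol set is not automatically conservative in a non-inferiority trial. If patients heading for stenosis drop out more often from the subclavian arm, the analysed difference shrinks and the upper confidence limit falls below 15 points too easily. This is the trial's single confirmatory claim, and no committed analysis would reveal the problem.

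**Working it through.** **Inputs from the document.** Jugular stenosis rate 10%, margin 15 points, one-sided 5%, 80% power, 50 analysed per group, at least 200 included (all {14}); misplacement 1.4% versus 9.1% (Background). An equal 10% rate in the subclavian arm is implied by the calculation.

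**Step 1: the plan's own figure.** n = (1.645 + 0.842)² × 2 × 0.10 × 0.90 / 0.15² = 49.5, so 50 per group. Power at 50 is 80.4%. The stated figure reproduces. The expected loss is (200 − 100)/200 = 50%.

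**Step 2: can the extreme-case scenarios rescue the result?** Suppose 100 randomised and 50 analysed per arm, with 5/50 events in each.

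- Per-protocol: difference 0, SE = √(2 × 0.09/50) = 0.060, upper limit 1.645 × 0.060 = 9.9 points. Non-inferior.
- Worst–best: 55/100 versus 5/100, difference +50 points, upper limit 58.9.
- Best–worst: 5/100 versus 55/100, difference −50 points.

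A range of about 100 points neither supports nor refutes anything.

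**Step 3: how different must the unseen patients be?** Same data, unseen jugular patients held at 10% (assumed), combined over 100 per arm:

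| Unseen subclavian rate (assumed) | Difference | Upper limit | Below 15? |
|---|---|---|---|
| 10% | 0 | 7.0 | yes |
| 20% | 5 | 12.7 | yes |
| 30% | 10 | 18.2 | no |
| 40% | 15 | 23.7 | no |

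The conclusion reverses somewhere between 20% and 30%, below the 42% historical subclavian rate quoted in {14}.

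**Step 4: risk of a false claim.** Set the true as-randomised rates at 25% versus 10%, exactly on the margin. Half the subclavian arm is analysed, so the excluded rate is 2 × 25% minus the analysed rate. The chance that the Wald upper limit falls below 15 points, by exact binomial enumeration with 50 per arm and the analysed jugular rate at 10%, is:

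| Analysed subclavian rate | Excluded subclavian rate | Chance of claiming non-inferiority |
|---|---|---|
| 25% (no selection) | 25% | 5.8% |
| 20% | 30% | 19% |
| 15% | 35% | 47% |

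**Step 5: one-arm or two-arm selection.** Assume 35% of patients with stenosis and 55% of the others are retained.

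- Subclavian: 0.25 × 0.35 / (0.25 × 0.35 + 0.75 × 0.55) = 0.0875/0.500 = 17.5%.
- Jugular, if the same applies: 0.10 × 0.35 / (0.10 × 0.35 + 0.90 × 0.55) = 0.035/0.530 = 6.6%.
- Selection in the subclavian arm only (17.5% versus 10%): false-claim risk 31% (Wald).
- Selection in both arms (17.5% versus 6.6%): about 18%.

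**Step 6: misplacement alone.** If every misplacement became an exit and all other patients had a 10% rate, the as-randomised difference would be (0.091 − 0.014) × (r − 0.10), where r is the stenosis rate among those exiting. For r from 25% to 100% (assumed) this is 1.2 to 6.9 points. Misplacement by itself moves the result little.

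**The case against.** The strongest defence is that the question is conditional. The Hypothesis concerns stenosis after use of the catheter for at least 7 days, and the Discussion presents the trial as proof of concept rather than an evaluation of routine practice. Removing failed placements and short dwell implements that question. Patients never catheterised in the allocated vein say little about stenosis from using it, and including short exposures dilutes the contrast. For example, if 30% of patients had short or no exposure and the same rate in both arms (assumed), a 15-point difference would become 0.70 × 15 = 10.5. This stands, and it is why per-protocol should remain primary. It does not make dwell time or CT completion independent of route.

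Second, much of the loss (death, low eGFR without dialysis, short need for the catheter) may be unrelated to route. The misplacement figures are historical, whereas this trial uses ultrasound guidance of the guidewire. This also stands: bias is possible, not shown.

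A reader might infer more than the document supports:

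- *That reporting non-completion is the only safeguard.* It is not. Section {20c} allows extreme-case scenarios and {20b} a stratified comparison. The former are optional and uninformative at 50% missing. The latter addresses measured baseline imbalance and cannot correct selection by outcome.
- *That the false-claim risk is about 30%.* That figure needs assumed retention rates acting in the subclavian arm alone. The document gives no retention rates by outcome.
- *That the stopping rule undercuts power.* The abstract says "Inclusion continues until 50 patients in each group have undergone a follow-up CT venography", and some scanned patients are not evaluable. But {14} describes the 100 CTs as serving the per-protocol analysis, and {20a} ties enrolment to the calculated sample size. This is a wording mismatch.

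**Conclusion.** The concern holds in a limited form. The plan makes its sole confirmatory claim on a set expected to be about half of those randomised, formed by post-randomisation events that can depend on route or on early venous damage. It commits to no analysis able to test whether that matters.

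The possible size is material. With true rates on the margin, assumed selection that lowers the analysed subclavian rate to 15–20% raises the false-claim risk from 5.8% to about 19–47%; the assumed 35%/55% retention in both arms gives about 18%. All of these rest on assumed selection and a Wald limit, and they illustrate sensitivity rather than predict the error rate. The document does not show that the trial is biased, nor that per-protocol is the wrong primary set for its stated question.

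**What to change.** 1. Keep the per-protocol analysis as primary for the question of at least 7 days' use.
2. Pre-specify a supportive analysis by allocated vein that uses every follow-up CT obtained, regardless of dwell time, tip location, crossover or additional catheter.
3. Replace the optional wording in {20c} with a committed multiple-imputation or tipping-point analysis for patients without a CT. A tipping-point analysis as in Step 3 shows readers how different the unseen patients must be before the conclusion changes.
4. Describe non-inferiority as robust only if the supportive analysis is consistent with the per-protocol result. A formal requirement that both succeed is debatable and is not needed here.
5. State in the abstract that the 50 per group are per-protocol-evaluable patients, as {14} implies.

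The cost is plan wording and extra analysis work. The supportive analysis will be diluted by short-exposure patients, imputation for so many patients leans on assumptions that cannot be verified, and the claim may have to be stated less firmly. The sample size does not change. Scanning patients who exit for failed placement or tip location would add information, but it means extra CTs and a definition of the imaging window and vessel segment for them. It is not required for this fix.

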### Baseline variables

Continuous variables following a symmetric distribution will be presented with mean (SD), while skewed variables will be presented with median (IQR). Ordinal variables will be presented with median (IQR) and categorical variables will be presented as *n* (%).

The primary outcome will be analysed as a binary variable (stenosis *vs* no stenosis) at follow-up and described using a 95% one-sided confidence interval for the absolute difference between the proportions, calculated as event rate intervention group − event rate control group. If the upper limit of the confidence interval is below the non-inferiority margin, the conclusion will be that the event rate in the intervention group is non-inferior to the event rate in the control group.

### Interim analyses {21b}

No interim analyses are planned for the current study.

### Methods for additional analyses (e.g. subgroup analyses) {20b}

As the sample size is not very large, there is a risk for imbalance in baseline characteristics between groups. This possible imbalance will be tested in a sensitivity test using univariate analyses. If needed, a comparison of the primary outcome between the groups will then be performed with a test where baseline characteristics can be stratified (e.g. the Cochran-Mantel–Haenszel test).

The Wilcoxon rank-sum test will be used to examine if the time until the CT venography differs between the groups.

Evaluation of the US/Doppler method will be made only in patients having undergone both an US/Doppler examination and CT venography. Sensitivity and specificity for the US-based method as compared to the golden standard, CT venography, will be determined and presented along with 95% confidence intervals. This will be performed for both intervention groups pooled together.

For all other secondary outcomes (the patients’ experience of the catheterisation, catheter blood flow during dialysis, catheter-related dialysis dysfunction, mechanical complications), data are expressed as mean (SD) or median and range. Qualitative variables are expressed as frequency with percentage. The *χ*^2^ test (or Fisher’s exact test as appropriate) will be used for comparison of categorical variables whereas the Student’s *t*-test and the Mann–Whitney *U* test will be used to compare continuous variables with normal and skewed distributions, respectively. A type 1 error rate of 5% will be used as threshold for statistical significance.

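### The adjusted sensitivity analysis is triggered by testing baseline imbalance and relies on a test of no difference, which cannot be set against the 15-point margin

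*Protocol article*

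**What the plan says.** The protocol article treats the primary outcome in two places.

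- **Primary rule** (Statistical methods, under the subheading Baseline variables). Stenosis is binary and is described with a "95% one-sided confidence interval for the absolute difference between the proportions", subclavian minus jugular. The conclusion is non-inferiority "If the upper limit of the confidence interval is below the non-inferiority margin". Sample size {14} sets that margin: "we chose a 15% noninferiority margin as this is less than half the absolute difference".
- **Supporting analysis** (Methods for additional analyses {20b}). The article notes that a trial of this size may be unbalanced at baseline and continues: "This possible imbalance will be tested in a sensitivity test using univariate analyses". Where this is judged necessary, the next step is stated as follows: "a comparison of the primary outcome between the groups will then be performed with a test where baseline characteristics can be stratified". CMH is the one example offered.

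Section {20b} names no covariate and does not say what makes adjustment needed. It mentions no adjusted difference and does not refer to the margin. Centre is the stratification factor for randomisation (Sequence generation {16a}) but is not mentioned as an adjustment factor.

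**The concern.** Two steps in {20b} do not fit a non-inferiority trial.

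**The question changes.** A CMH test asks whether the data contradict no association between route and stenosis. The trial asks whether an excess of 15 points can be excluded. Failing to reject equality is not evidence for the second statement, and with 50 patients per group it is easy to fail to reject. The p-value puts no limit on the absolute difference, so it cannot show whether adjustment strengthens or weakens the primary result, which is the purpose of a sensitivity analysis.

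**The trigger is the data.** Adjustment happens, and variables are picked, after looking for imbalance in the trial's own data. A variable can be unbalanced without being prognostic, or prognostic without being flagged. The adjusted result is then open to selection.

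This matters because the primary set is restricted to patients who completed the CT venography, about 100 out of at least 200 included. Loss on that scale can disturb the balance that randomisation gave, so readers will look to the adjusted result. It should be on the scale of the primary rule.

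**Working it through.** **Inputs.** From Sample size {14}: jugular incidence 10%, margin 15 points, one-sided 5%, power 80%, 50 per group. Assumptions: true subclavian incidence also 10% for the sample size; Wald limits; a two-sided 5% level for the test of equality. The 5% threshold in {20b} closes the paragraph on other secondary outcomes, so no level is stated for the adjusted test.

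**1. The plan's own figure.** n = (1.645 + 0.842)² × [0.10 × 0.90 + 0.10 × 0.90] / 0.15² = 6.183 × 0.18 / 0.0225 = 49.5, so 50 per group. This reproduces the plan.

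**2. The two criteria on the same data.** Fix jugular at 5/50. For subclavian proportion p, the upper limit is (p − 0.10) + 1.645 × √{[p(1 − p) + 0.09]/50}. The test of equality is z = (p − 0.10)/√{2q(1 − q)/50}, with q the pooled proportion.

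| Subclavian | Difference | Upper limit (points) | Non-inferior? | z | Two-sided p |
|---|---|---|---|---|---|
| 7/50 | 4 | 14.7 | yes | 0.62 | 0.54 |
| 8/50 | 6 | 17.0 | no | 0.89 | 0.37 |
| 12/50 | 14 | 26.1 | no | 1.86 | 0.062 |
| 13/50 | 16 | 28.4 | no | 2.08 | 0.037 |

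From 8 to 12 subclavian events, equality is not rejected and non-inferiority is not shown. The single-stratum Mantel-Haenszel chi-square, which multiplies z² by 99/100, gives p = 0.064 at 12/50 and 0.038 at 13/50, so the cut-off is the same.

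**3. How often the two criteria part.** Exact binomial enumeration at 50 per group, using the single-stratum Mantel-Haenszel chi-square without continuity correction:

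| True rates, jugular vs subclavian | Equality not rejected | Non-inferiority shown | Not rejected and not shown |
|---|---|---|---|
| 10% vs 10% | 0.95 | 0.81 | 0.17 |
| 10% vs 20% | 0.72 | 0.19 | 0.53 |
| 10% vs 25% (difference equals the margin) | 0.49 | 0.058 | 0.43 |

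**4. A stratified example (invented counts).** Two strata of 25 per group: subclavian 5/25 and 6/25, jugular 3/25 and 2/25.

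- CMH: observed minus expected = (5 − 4) + (6 − 4) = 3. Variance per stratum = 25 × 25 × 8 × 42/(50² × 49) = 1.714, total 3.429. Chi-square = 9/3.429 = 2.63, p = 0.105.
- Mantel-Haenszel risk difference: equal weights, (8 + 16)/2 = 12.0 points. Standard error = √[(0.010624 + 0.010240)/4] = 0.0722. Upper limit = 12.0 + 1.645 × 7.22 = 23.9 points.

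The test finds no significant difference, while the stratified difference shows that 15 points is far from excluded.

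**5. The trigger (illustration only).** If 10 independent baseline variables were each tested at 5%, chance alone would flag at least one with probability 1 − 0.95¹⁰ = 0.40. The number of variables, their independence and the level are all assumed.

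**The case against.** The strongest reply is that nothing hangs on this analysis. The decision rule is fixed elsewhere and is right, and {20b} concerns a conditional sensitivity analysis. That stands. A reader might infer that a non-significant CMH result could rescue a failed trial, but the documents do not support this: they give the stratified comparison no role in the conclusion.

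Second, CMH is only an example, and a Mantel-Haenszel risk difference belongs to the same stratified family. It would be wrong to say that the protocol binds itself to CMH. Still, the sentence asks for a test and not for an estimate with a limit, and its one example has the wrong null hypothesis.

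Third, covariates and estimators are commonly left to an SAP, which is not shown. Their absence is therefore not the criticism. The criticism is of what the article does state: a data-driven trigger followed by a test.

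Fourth, the reading of the trigger as significance testing is an inference from the words that imbalance will be tested with univariate analyses; no level is given. A reader might also take the 40% figure as a property of this trial, but it rests wholly on assumed inputs. Moreover, patients leave the primary set for reasons that may differ by route, such as failed placement in the assigned vein, so imbalance need not be mere chance. That is a good reason to display baseline data by group. It does not make a test the right trigger for adjustment.

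**Conclusion.** The point holds, limited to the supporting analysis. As worded, {20b} chooses the adjustment from the trial's data and then answers a question other than the trial's. With 5/50 jugular events, the mismatch covers 8 to 12 subclavian events, where upper limits run from 17 to 26 points. At true rates of 10% and 20%, the two criteria part in this way with probability 0.53. These figures assume 50 analysed per group, Wald limits, a two-sided 5% test and, in the enumeration, a single stratum. The difference between the two questions depends on none of these. The primary decision rule and the sample size are unaffected. The wording should be corrected, but the flaw does not threaten the trial's main conclusion.

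**What to change.** Replace the wording in {20b}, or settle it in the SAP, before anyone sees outcomes by group:

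1. Present baseline characteristics by group descriptively, for the analysed set. Do not use tests of imbalance to trigger adjustment.
2. Specify one adjusted sensitivity analysis, always performed, with a very small set of covariates named in advance and already collected. Centre is the natural first factor because randomisation was stratified by it. State in advance how small centres will be pooled.
3. Report a Mantel-Haenszel (stratified) risk difference with its one-sided 95% upper limit against 15 points, in place of the CMH p-value.

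Previous central venous catheterisation is a possible second factor, since the eligibility criteria allow it. The article does not say that it is recorded, so this must be checked first.

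The cost is wording only if the covariates are already in the eCRF; the sample size stays at 50 per group. The drawback is sparse data. At 10% incidence, 100 patients yield about 10 events, or about two per centre over five centres, and the article says at least five. A centre with analysed patients in only one group contributes nothing to the stratified estimate. The set must therefore stay minimal, and a logistic model with many terms should be avoided.
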